### Outcome measures

The primary outcome is health related quality of life assessed with the EQ-5D-5 L questioning list 12 months after initiation of ECS treatment.

The EQ-5D-5 L questioning list consists of a descriptive system with 5 domains (mobility, self-care, usual activities, pain/discomfort, anxiety/depression) with 5 possible levels on each which can be converted in to a single summary index score, which represents the societal perspective on quality of life (QoL), and a score on a visual analogue scale, which represents the patient’s perspective in QoL. The iMTA questionnaire is used to assess medical consumption at 6 and 12 months after initiation of ECLS treatment. The iPCQ questionnaire is used to assess productivity losses at 6 and 12 months after initiation of ECLS treatment.

Secondary outcome is one year survival. Additional measurements are EQ-5D-visual analog scale (VAS) score and societal costs. Same parameters are assessed at 6 months, and 1 month before ECLS treatment, the latter retrospectively provided at admission, if needed by relatives.

#### Subgroup analysis

In order to estimate cost-efficacy of ECLS based on indication patients will be categorized into six different subgroups: respiratory – bridge to recovery, respiratory – bridge to transplant, cardiac – bridge to recovery, cardiac – bridge to transplant, cardiac – post-cardiotomy, and extracorporeal cardiopulmonary resuscitation.

#### Sample size calculation

Sample size calculation is based on survival with a good health related-QoL assessed with the EQ-5D-VAS questionnaire one year after initiation of ECLS treatment. Predicted mortality in usual care is 80%. Overall, expected mortality in patients with ECLS treatment is 38%. The increase in survival is thus 42%. To demonstrate an effect on survival 25 patients are needed: risk ratio 0.48 (95%CI 0.28–0.82). In usual care 90% will have a poor outcome, for sake of power analysis defined as dead or an EQ-5D-VAS below the median. With ECLS treatment this will be 69% so 132 patients are needed to demonstrate an effect on QoL. To compensate for a 5% less effect and 5% drop-outs 210 patients will be enrolled to include 200 patients with complete follow-up in the final analysis (RR 0.82; 95%CI 0.75–0.90). Based on a 38% mortality and a study duration of 3 years, 124 (62% out of 200) patients have a complete one year follow-up at the end of the study.

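### The sample size rests on a composite whose planning rates follow from mortality alone, so it cannot show an effect on quality of life against usual care, and the declared primary outcome has no stated precision

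*Protocol article*

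**What the plan says.** In the protocol article, the section Outcome measures declares the main endpoint as follows: "The primary outcome is health related quality of life assessed with the EQ-5D-5 L questioning list 12 months after initiation of ECS treatment". Mortality ranks below it: "Secondary outcome is one year survival". The VAS is placed lower still: "Additional measurements are EQ-5D-visual analog scale (VAS) score and societal costs". The same section describes the EQ-5D-5L as a five-domain descriptive system, converted to an index, together with a VAS score.

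The section Sample size calculation uses a different target: being alive at one year with a good VAS rating. The mortality inputs, in per cent, are "Predicted mortality in usual care is 80" and "expected mortality in patients with ECLS treatment is 38". A poor outcome is "for sake of power analysis defined as dead or an EQ-5D-VAS below the median", set at 90% in usual care and 69% with ECLS. From these rates the paragraph derives 132 patients and says this number serves to demonstrate an effect on quality of life. After allowing for a 5% smaller effect and 5% drop-out it enrols 210, so that 200 have complete follow-up. It then states that "124 (62% out of 200) patients have a complete one year follow-up at the end of the study".

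The Ethics and Statistics sections give the comparator: each patient's predicted mortality when ECLS is started. No usual-care patients are followed.

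**The concern.** Three features of the plan do not fit together.

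- The variable that is sized (death combined with a dichotomised VAS) is not the variable declared primary (the EQ-5D-5L at 12 months, with no death component).
- The two poor-outcome rates look like mortality plus half of the survivors. If so, they carry no information on quality of life.
- The usual-care rate needs a VAS distribution in usual-care survivors, which the design neither observes nor predicts.

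At stake is what the sample size can be said to support. Anyone relying on the paragraph would believe that the study is powered for quality of life against usual care, and that its primary outcome has been sized. Neither would be true.

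**Working it through.** **Inputs** (Sample size calculation): mortality m = 0.80 in usual care and 0.38 with ECLS; poor outcome 0.90 and 0.69; 132 patients; 200 analysed; 124 survivors. Alpha, sidedness and power are not stated. Two-sided 5% and 80% power are inferred because they reproduce the plan's numbers.

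**1. Reproduce the plan's figures.** The formula is for two independent proportions, with continuity correction.
- 0.90 vs 0.69: 57 per group uncorrected, 66 corrected. 2 × 66 = 132, an exact match.
- 0.80 vs 0.38: 21 per group uncorrected, 25 corrected. This matches the stated 25, as a per-group number.
- Risk ratio for 0.90 vs 0.74 (69% plus 5 points) with 200 vs 200: 0.822 (0.748 to 0.903). The plan states 0.82 (0.75 to 0.90).

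So 132 follows from the rates used. The question is what those rates represent.

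**2. Where the rates come from.** If half of the survivors fall below the median, P(poor) = m + 0.5(1 − m) = (1 + m)/2.
- Usual care: (1 + 0.80)/2 = 0.90.
- ECLS: (1 + 0.38)/2 = 0.69.
- Difference: 0.90 − 0.69 = 0.21 = (0.80 − 0.38)/2.

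Both planning rates are functions of mortality only. Survivors are split 50:50 in both groups, so no difference in quality of life is assumed.

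**3. What the composite responds to.** Let g be the share of ECLS survivors above the cut-off, with usual care held at 50%. Then P(poor | ECLS) = 1 − 0.62g. Power is two-sided 5%, no continuity correction, 200 per group (the basis that reproduces the plan's interval).

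| g | Poor outcome, ECLS | Poor outcome, usual care | Power to declare benefit |
|---|---|---|---|
| 0.50 | 69.0% | 90% | >99.9% |
| 0.40 | 75.2% | 90% | 97.6% |
| 0.30 | 81.4% | 90% | 69% |

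The direction reverses only when 0.62g < 0.10, that is g below about 0.16. ECLS survivors could fare clearly worse than usual-care survivors and the composite would still favour ECLS, because mortality drives it.

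**4. Whose median?** The article does not say.
- Median of the study's own survivors: half fall below it by construction (ties aside), so the observed ECLS rate is also (1 + m)/2.
- External median: the observed ECLS rate can move with quality of life. The usual-care rate is still predicted mortality plus an assumed 50% of survivors.

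Under either reading, an effect on quality of life against usual care is not identified.

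**5. Precision of the declared primary outcome.** Expected survivors: 0.62 × 200 = 124. The half-width of a 95% interval for the mean index is 1.96 × SD/√124. The article gives no SD, so a range is assumed.
- SD 0.20: 0.035
- SD 0.25: 0.044
- SD 0.30: 0.053

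**The case against.** The composite is introduced only for the power calculation; it is not listed as an outcome, and the Statistics and cost-effectiveness sections do not analyse it. The VAS belongs to the EQ-5D-5L instrument. Survival is a secondary outcome, and the QALY work combines survival with quality of life. About 124 survivors would estimate the mean index quite well.

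Much of this stands, and it rules out several stronger readings that a reader might infer:

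- *The composite is always a fixed function of mortality.* This is exact for the planning rates. For observed data it holds only if the median is that of the study's own survivors.
- *The VAS is an unrelated instrument.* It is part of the EQ-5D-5L. The mismatch is between a composite of death and a dichotomised VAS, and the EQ-5D-5L itself.
- *No VAS exists without ECLS.* Values for one month before ECLS are collected. What is missing is a VAS under usual care.
- *The counts of 200 and 124 contradict each other.* Deaths count in the composite, so 200 patients can have a known composite status while about 124 supply the questionnaire. The 124 is an expectation at 38% mortality and not a ceiling.
- *The sample is too small for the primary outcome, or that outcome must be replaced.* Step 5 shows no shortfall. Scoring death as 0 would change the estimand. It would also be driven mainly by mortality: treating the expected median of 0.83 as a mean, the mortality term 0.62 × 0.38 × 0.83² = 0.162 is 81 to 87% of the variance at an SD of 0.25 to 0.20.

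The objection does not rescue the stated purpose of the 132. Saying that the composite serves only the power calculation concedes that the primary outcome was not sized.

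**Conclusion.** The point holds, and the claim is wrong as written. The 21-point difference behind the 132, and behind the 200 derived from it, is exactly half of the 42-point mortality difference. With predicted mortality as the only comparator, these numbers size a diluted survival contrast and cannot demonstrate an effect on quality of life. The sized variable also differs from the declared primary outcome, for which no precision is given.

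The identity is arithmetic on the plan's own figures and needs no assumption. The match to 132 rests on the inferred two-sided 5% level, 80% power and continuity correction. The half-widths rest on an assumed SD. The fault lies in what the paragraph claims; the documents do not show that 200 patients are too few, or that the composite will be reported as a quality-of-life result.

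**What to change.** - Remove the claim that 132 patients show an effect on quality of life relative to usual care. Describe 132 and 200 as sizing for a survival-driven composite.
- If the composite is kept, replace the unspecified median with a fixed external cut-off set before data are seen.
- State the sizing of the primary outcome as precision among the expected 124 or so survivors: a 95% half-width of about 0.035 to 0.044 for the mean index at an SD of 0.20 to 0.25, with the SD declared as an assumption.
- Say that 200 patients are to have a known composite status and about 124 are expected to supply the EQ-5D-5L.
- Report one-year survival beside the survivors-only result. An all-patient index with death scored 0, in line with the planned QALY calculation, can be added as a supportive analysis and need not replace the primary outcome.

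The cost is rewording the sample size and outcome sections, with no extra patients or data. The downside is that the sample size paragraph then makes a weaker claim.

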#### Statistics

With the additional information on costs (apart from direct hospital costs already available) assessed within this study it is now possible to calculate the costs of ECLS therapy related to mortality. Based on case-fatality and health related-QoL we will be able to assess QALY’s. For this calculation the predicted mortality at initiation of ECLS therapy is used for comparison. Many patients treated with ECLS survive only after lung transplantation, heart transplantation or implantation of a left ventricular assist device. Life expectancy of the study population can thus be based on the average expectations of that particular patient category. The remaining patients who were treated with ECLS as a bridge to recovery have a reasonable good quality of life [10, 12]. Based on our follow-up study of ICU patients we expect that the median health related-QoL in surviving patients will be 0.83 after one year, which results in 0.36 QALY gained per treated patient. Although additional total healthcare costs and loss of income will be substantial and assumed to exceed €172,200 after one year compared with usual care, lifetime-predicted costs and QALYs is expected to be cost-effective due to the relatively good life-expectancy of survivors. With data from 200 patients of which 62% survive until one-year follow-up we will be able to make a statement about cost-effectiveness for all indications for ECLS.

A cost effectiveness analysis as well as a Budget Impact Analysis will be performed in accordance with the Dutch guidelines [13, 14].

#### Cost effectiveness analysis (CEA)

In the economic evaluation, the primary aim will be to estimate societal costs of ECLS utilization. The secondary aim will be to estimate the cost effectiveness and cost utility of ECLS utilization compared to usual care (from a societal perspective). The cost effectiveness analysis will be performed based on survival. The costs utility analysis will be performed based on EuroQol (EQ-5D-5 L) defined utilities. Results of the cost utility analysis will display the extra costs or savings of ECLS, in order to gain one QALY, compared to usual care. The time horizon of this clinical study will be 1 year, therefore the analysis will not include discounting of costs and effects. Scenario analyses are planned within the trial based evaluation as well as in the model that estimated the effects over a life time horizon. Bootstrap re-sampling will be performed on the cost and effect pairs in order to calculate confidence intervals. Furthermore, cost effectiveness acceptability curves will be plotted, to estimate the probability that ECLS is more cost-effective than usual care, for different amounts of money that a decision maker may be willing to pay for one additional QALY. The trial based results of the CEA, together with available data from literature, will be extrapolated to a life time horizon, using decision modeling in a secondary analysis.

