## Methods/design

The design is a multi-center prospective observational cohort study with the aim to assess the health-related quality of life after ECLS treatment and the associated costs. We expect that survivors of ECLS therapy have a good quality of life and life expectancy. Lifetime predicted costs for QALYs are expected to be cost-effective. Therefore our hypothesis is that ECLS treatment is cost effective.

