### Inclusion criteria

All adult patients who receive ECLS will be included. With our consortium we cover nearly all ECLS treatments in The Netherlands. In general, according to the ELSO guidelines, ECLS can be considered in acute severe heart and/or lung failure with high mortality risk despite optimal conventional therapy. ECLS is indicated in most circumstances at 80% mortality risk. Severity of illness and mortality risk is measured as precisely as possible using measurements for the appropriate age group and organ failure.

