### Ethics

The need for ethical approval was waived by the institutional medical ethics board of the University Medical Center of Groningen (protocol number METc 2017/196), and written informed consent will be obtained from all patients or legal representatives.

The predicted mortality for every patient at the initiation of ECLS is used and compared with the actual mortality at one year of each patient. That means that every patient acts as his own control. Depending on the indication or the underlying disease, the APACHE-4, SOFA score, RESP score, or SAVE score will be used to estimate mortality. Although the used models predict hospital mortality instead of one year mortality, the vast majority of mortality is during hospital admission, so the used mortality prediction is expected to be valid for one year survival analyses as well [10, 11].

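### Bootstrapping the ECLS patients' cost-effect pairs leaves out error in the predicted usual-care comparator, so the incremental intervals will be too narrow and the acceptability curves too steep

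*Protocol article*

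**What the plan says.** All references are to the protocol article.

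- **Who is studied.** Methods/design: "The design is a multi-center prospective observational cohort study". Inclusion criteria: "All adult patients who receive ECLS will be included". There is no usual-care group.
- **What stands in for usual care.** The Ethics section says: "The predicted mortality for every patient at the initiation of ECLS is used and compared with the actual mortality at one year of each patient". It then adds: "That means that every patient acts as his own control". The Statistics section carries the same comparator into the QALY calculation: "For this calculation the predicted mortality at initiation of ECLS therapy is used for comparison".
- **What the prediction measures.** The Ethics section opens its justification with "Although the used models predict hospital mortality instead of one year mortality" and goes on to expect validity at one year because most deaths occur in hospital. No error is attached to that step.
- **How uncertainty is to be expressed.** Cost effectiveness analysis (CEA): "Bootstrap re-sampling will be performed on the cost and effect pairs in order to calculate confidence intervals". Acceptability curves are then plotted "to estimate the probability that ECLS is more cost-effective than usual care". Scenario analyses are also announced, without saying what they vary.
- **Where costs and utilities come from.** Outcome measures, Cost analysis and Patient outcome analysis describe collection from enrolled patients. No source is named for usual-care cost or for the utility of usual-care survivors.

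**The concern.** An incremental cost, an incremental QALY, an ICER and an acceptability curve each depend on two sides, and their variance should reflect both. Here one side is sampled and the other is modelled or assumed. A bootstrap of the sampled side reproduces the sampling error of the ECLS cohort. It treats as correct the scoring models that supply usual-care mortality, their use at one year, and whatever values are inserted for usual-care cost and utility.

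The article names the interval method and the comparison it serves, so this goes beyond detail left to an analysis plan. Cost-effectiveness is the stated hypothesis in Methods/design, and the Abstract says that confirming it could broaden ECLS use. Intervals and probabilities that leave out error in the least certain input would overstate how firmly the study supports that conclusion. A larger cohort would not cure this, because sampling error shrinks with n and model error does not.

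**Working it through.** **Inputs from the article.** Usual-care mortality 80%, ECLS mortality 38%, 200 patients analysed, poor outcome 90% against 69% (Sample size calculation). Utility 0.83, QALY gain 0.36, and one-year extra cost assumed to exceed EUR 172,200 (Statistics).

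**Inputs assumed here.** The SD of the error in mean predicted mortality is set at 2, 3, 5 and 10 points and taken as independent of sampling error. Patient-level cost SD, used in step 5 only, is EUR 100,000.

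**1. The plan's own figures.**
- Poor outcome 90% against 69%, at two-sided 5%, 80% power and with continuity correction, gives 66 per arm, or 132 in two arms. This matches the stated 132. Alpha and power are not stated; these values reproduce the figure.
- I read the 5% smaller effect as 74% poor outcome. Then RR = 0.74/0.90 = 0.822.
- With a sampled usual-care arm of 200, SE(log RR) = sqrt(0.26/(0.74 x 200) + 0.10/(0.90 x 200)) = 0.0481. The interval is 0.748 to 0.903, which matches the stated 0.75 to 0.90.
- With a fixed comparator only the first term remains and the interval is 0.757 to 0.893, which does not match.
- So the sample size section gives usual care a sampling variance that the bootstrap has no patients to supply.
- QALY gain: 0.42 x 0.83 = 0.349, close to the stated 0.36. The difference does not affect this point.

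**2. What resampling the predicted risk adds.** In a simulation with n = 200, between-patient SD of predicted risk from 0.05 to 0.20, and death risk rising 0.8 points per point of predicted risk (all assumed):
- The usual-care side varies, with SE up to 0.012 QALY.
- The SE of the QALY difference is 0.0272 to 0.0283, against 0.0284 with fixed risk.
- The variation is case mix and does not widen the incremental interval.

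**3. What error in the prediction adds.** SE of incremental survival = sqrt(0.62 x 0.38/200 + SD^2).

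| SD of mean predicted mortality | SE | Ratio to fixed comparator | 95% interval |
|---|---|---|---|
| 0 (fixed) | 0.034 | 1.00 | 0.353 to 0.487 |
| 2 points | 0.040 | 1.16 | 0.342 to 0.498 |
| 3 points | 0.046 | 1.33 | 0.331 to 0.509 |
| 5 points | 0.061 | 1.77 | 0.301 to 0.539 |
| 10 points | 0.106 | 3.08 | 0.213 to 0.627 |

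For scale, a real control group of 200 at 80% mortality would give sqrt(0.62 x 0.38/200 + 0.80 x 0.20/200) = 0.044, or 1.30 times.

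**4. Sensitivity of the point estimate (a separate matter from interval width).** ICER = 172,200 / (0.83 x (usual-care mortality - 0.38)).
- 70%: 172,200/0.2656 = about EUR 648,000 per QALY
- 80%: 172,200/0.3486 = about EUR 494,000
- 90%: 172,200/0.4316 = about EUR 399,000

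**5. Illustration on the ICER and the curve (one year, assumed cost SD).** The 95% ICER interval is about EUR 416,000 to 598,000 with usual care fixed, 380,000 to 695,000 at SD 5 points, and 332,000 to 977,000 at SD 10 points. For the same three cases, the probability of cost-effectiveness is 0.15, 0.26 and 0.35 at EUR 450,000 per QALY, and 0.87, 0.75 and 0.66 at EUR 550,000. The curve flattens on both sides of the point estimate.

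**The case against.** The strongest reply has four parts.

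**The comparator need not be a constant.** Each patient has an individual predicted risk, which can be resampled with the patient. This stands. A reader might infer that usual care carries no variability at all, and the article does not support that. Step 2 shows, however, that the variability is case mix and does not replace model error.

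**The size is not documented.** This also stands. A reader might infer that the intervals are far too narrow, or that the curves will show near-certainty. The article gives no calibration error. At an SD of 2 to 3 points the understatement is 1.16 to 1.33 times, about what a real control arm of 200 would add. Larger factors need 5 to 10 points. Nominal 95% coverage works out at 73% for 5 points and 48% for 10, but only for the survival difference. A bootstrap that also resamples costs and utilities carries other variance, so these are not coverages of an ICER interval or a curve.

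**Shifting usual-care mortality moves the estimate, not its variance.** Correct. The ICERs at 70%, 80% and 90% show sensitivity of the point estimate and are no measure of interval width. They also hold EUR 172,200 fixed, although the article defines that sum relative to usual care, so it could change with usual-care survival.

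**The article is condensed, and scenario analyses are planned.** Input distributions can properly be left to an analysis plan, and a scenario on usual-care mortality would fit among those planned. But the article does say which procedure produces the intervals, and that procedure cannot carry comparator error. Scenarios would sit beside the intervals and curves without altering either.

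**Conclusion.** The concern holds in a limited form. The stated bootstrap omits error in predicted usual-care mortality, in the hospital-to-one-year step, and in unobserved usual-care cost and utility. The direction follows from the design: incremental intervals too narrow and acceptability curves too steep. The amount is not known from the article. It is about 1.2 to 3.1 times on the SE of incremental survival for an assumed SD of 2 to 10 points, independent of sampling error.

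This should be fixed, but it does not undermine the study. Comparative cost-effectiveness is the secondary economic aim, behind estimating societal costs. Enrolment, data collection and the EQ-5D-5L primary outcome are untouched. It still deserves attention because it bears directly on the stated hypothesis.

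**What to change.** Before the data are analysed, amend the CEA section or the analysis plan as follows.

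1. In each bootstrap replicate, resample ECLS patients with their predicted risks. Also draw (a) usual-care mortality, with calibration error of the scores and the conversion from hospital to one-year mortality; (b) usual-care cost; and (c) utility of usual-care survivors. Beta distributions for the first and third and a gamma for the second would do. Give a source for each distribution and its spread.
2. Build the confidence intervals and acceptability curves from these joint draws.
3. Report a one-way or threshold analysis of the ICER over usual-care mortality, letting the incremental cost change with usual-care survival where the data allow.

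The cost is a few lines of text, some programming and the work of sourcing the inputs. No further patients or data collection are needed. The price is wider, less favourable intervals whose width depends on the chosen input distributions, which is why their sources should be fixed in advance.
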